#### Biological indicators of risk

Laboratory analysis will include fasting total cholesterol (mg/dl), HDL and LDL cholesterol (mg/dl), triglycerides (mg/dl), and glycosylated haemoglobin (%). Each blood sample will be analyzed by a certified laboratory.

Resting blood pressure will be assessed via an aneroid sphygmomanometer. Exercise capability will be considered the maximal power (Watts) reached during an incremental bicycle stress test. Moreover, an additional index of oxygen consumption, the double product, will be calculated as a heart rate x systolic blood pressure product.

#### Psychological well-being

Psychological health will be measured by the Psychological General Well-Being Index [55], validated in Italian [56]. The PGWB is a self-administered questionnaire composed by six sub-scales: anxiety, depression, positive well-being, self-control, general health and vitality. Higher scores indicate better health.

#### Quality of life

Health-related quality of life will be assessed by the SF36 questionnaire [57]. It is a widely used self-report instrument validated in Italian [58], which is composed by eight sub-scales: physical function, physical role, general health, social function, experience of pain, mental health, and emotional role and vitality. Physical component summary (PCS) and mental component summary (MCS) measures [59] will be used inlieu of the eight dimensions of the SF-36 to reduce the number of statistical comparisons and type 2 error. Higher scores indicate better quality of life.

#### Dietary habits

The Mediterranean diet has received support for the primary prevention of acute coronary syndrome [60,61]. Results from the CARDIO2000 study [62] showed an inverse association of such dietary pattern with serum lipids, blood pressures, inflammation, and coagulation markers related to cardiovascular disease. Moreover, individuals with higher scores of adherence to the Mediterranean diet were less likely to have acute coronary syndrome [60]. Since several studies have suggested that dietary patterns are more predictive of disease risk and mortality than individual foods or nutrients [63,64], an overall diet assessment will be assessed through the Mediterranean Diet Score [62], based on inherent characteristics of the Mediterranean diet. Questions focus on the frequency of usual consumption of 11 main components of the Mediterranean diet and each item is scored on an ordinal scale from 0 to 5. Scores are summed to obtain a total score ranging from 0 to 55.

#### Exercise

Participants’ physical activity levels will be measured by The International Physical Activity Questionnaire (IPAQ) [65], a self-report questionnaire that assesses the number of days per week and the number of times per day an individual spends doing specific activities. The questionnaire consists of 5 categories: job-related physical activity, transportation physical activity, housework, household tasks including family-care, recreation, sport and leisure time, and time spent sitting. In order for an activity to be reported, a minimum of 10 continuous minutes must be spent doing the activity.

#### Smoking status

Self-reports of smoking status were collected from participants at the end of treatment and at 6- and 12-months follow-up. The actual smokers will be also asked to report the average number of cigarettes smoked per day. The 7-day point prevalence abstinence rate at each assessment point will be used to assess the change of smoking status over time.

#### Adherence to medication

Adherence to pharmacological treatment will be measured by the Morisky Medical Adherence scale-8 items (MMAS) [66] that was developed from a previously validated four item scale [67] and supplemented with additional items addressing 1) the factors that may affect adherence 2) the circumstances surrounding adherence behavior and 3) problems with the complexity of the medical regimen The MMAS has a dichotomous response category for each item and a 5-point Likert response for the last item (“How often do you have difficulty remembering to take all your medication?”). Higher scores indicate lower adherence. The measure has proven to be reliable (α = 0.83) and has shown good concurrent and predictive validity [66]. The Italian version of the scale has been recently validated [68].

#### Psychological inflexibility

Psychological inflexibility will be measured through the Acceptance and Action Questionnaire-II [69]. The Italian version of the questionnaire has shown good reliability (α = 0.83) and high convergent validity [70]. Furthermore, disease-specific psychological inflexibility will be measured using the Cardiovascular Disease Acceptance and Action Questionnaire (CVD-AAQ), created for the proposed investigation. The CVD-AAQ was created by refocusing items from the AAQ-II [69] toward cardiovascular disease. The CVD-AAQ measures acceptance of thoughts and feelings related to cardio-vascular illness and the degree to which they interfere with valued action. It consists of 7 Likert-type items and showed good reliability in a preliminary study with 258 cardiac patients. Correlations with the AAQ-II [69] provide preliminary support for the convergent validity of the CVD-AAQ. Moreover, CVD-specific in flexibility is inversely associated with measures of psychological well-being and medication adherence.

### Sample size

The primary outcome variables of this study are the mean changes on the following indicators: LDL-cholesterol, resting systolic blood pressure, body mass index, and psychological well-being measured by the PGW.

As outlined above, at the time of the study’s design, we were unable to project the level of improvement on these outcome measures as effect of the ACT intervention over a 12 months follow-up period, since no data on cardiac patients were available.

Hypothesizing a medium effect size of the ACT intervention (in particular a standardized effect of at least 0.3 standard deviations) the following between-group differences on mean changes from baseline to 12-month follow-up are expected: 8.8 mg/dl in LDL cholesterol, 4 mmHg on systolic resting blood pressure and 1.3 kg/m^2^ in BMI. According to general guidelines, a power level of .80 is considered adequate to detect treatment effects [71]. In accordance with deJong and colleagues [72], a clustered design will require 160 participants to detect medium treatment effects with a statistical power of 0.8 and a significance level of .05.

Assuming a drop-out rate of <5% (as found in the GOSPEL study [51]), a sample size of 168 participants was finally defined, resulting in 84 participants being randomly assigned to each group.

Data on “lost to follow-up” participants will be analyzed to identify any relevant characteristics that may differ from the remainder of the study group. All data for the primary and secondary outcome measures will be analyzed using an intention-to-treat analysis such that participants will remain in their randomly assigned groups at final analysis, regardless of actual participation within such group.

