**Methods:**

Approximately 168 patients will be recruited from an outpatient cardiac rehabilitation unit and randomly assigned to receive usual care or usual care + a brief ACT-based intervention. The ACT group will be administered five group therapy sessions integrating educational topics on heart-healthy behaviours with acceptance and mindfulness skills. Participants will be assessed at baseline, six weeks later (post treatment for the ACT condition), at six and twelve months follow-up.

A partially-nested design will be used to balance effects due to clustering of participants into small therapy groups. Primary outcome measures will include biological indicators of cardiovascular risk and self-reported psychological well-being. Treatment effects will be tested via multilevel modeling after which the mediational role of psychological flexibility will be evaluated.

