### Assessment procedure

Participants will be asked to complete all study measures before randomization. Follow-up repeated measures assessment will be completed on all study participants six weeks later (post treatment), and at 6- and 12-month follow-up.

Demographic data such as gender, age, marital status, level of education, and employment status will be assessed in order to control for these potential confounders.

Medical data such as recurrence of cardiac events and additional diagnoses (e.g. diabetes) that may confound results will be retrieved from clinical records. Furthermore, a listing of participants’ current medications and dosages at each time point will be used to assess the degree to which the intervention is affecting change above and beyond medication effects.

Participants in both groups will provide a history of any psychological treatment or counselling to assess potential familiarity with mindfulness- and acceptance-based therapies.

A range of physiological and psychological outcome measures will assess the following: modifiable cardiovascular risk factors, adherence to medication and recommended life-style, and psychological well-being and quality of life.

Adjusted change scores for all the outcome measures will be calculated in order to assess the interventions ability to produce changes over time.

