### Randomization procedure and blinding

After the baseline assessment, participants are randomized to either ACTonHEART or usual care with the condition assignment determined via a computer generated algorithm. A block randomization scheme is employed, balancing gender and baseline impact of modifiable cardiovascular risk factors assessed using the INTERHEART Modifiable Risk Score (highest tertile vs. middle tertile). Participants allocated to the ACT condition are then scheduled into treatment groups. Randomization and follow-up assessments will be administered by independent practitioners blind to condition assignment and research hypotheses.

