### Statistical analysis

Preliminary analyses will be conducted to test parametric statistical assumptions. If strong violations are detected, robust methods or data transformation will be applied. Outcome measures will be examined with intention-to treat analyses and analyses will be conducted on treatment completers.

Since participants in the ACT condition will be clustered into small therapy groups, the between-group variance should be taken into account. In fact, it has been shown that ignoring this level of nesting in the data can affect estimated variances and power to detect treatment and covariate effects [73], significantly inflate the Type I error rate and treatment effect size [74]. Thus, given the partially-nested design of this study, data will be analysed according to the guidelines suggested by Daniel J. Bauer and colleagues in their seminal paper [75]. Two-tailed tests with an adjusted critical alpha of 0.01 (0.05/4) will be conducted for examining the treatment effects on the four primary outcomes. Furthermore, on the basis of the best multilevel model structured in the primary analyses, the moderating effects of some putative covariates such as gender, age, level of education, marital status, cardiovascular disease status, and diabetes, will be explored and no adjustment to alpha will be applied. Beyond these analyses we also intend to explore the effects of ACT on measures of dietary habits and physical activity, smoking cessation, medication adherence and health-related quality of life, exercise capability during an incremental bicycle stress test, lipid profile, glycosylated haemoglobin level, and waist to hip ratio. The mediating role of psychological inflexibility will also be examined within the structured multilevel model. The MLwiN 2.21 sofware (Centre for Multilevel Modeling-CMM, University of Bristol) will be used for data analysis.

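### Primary outcomes are mean changes, but the article leaves the adjustment undefined and names neither the outcome's baseline value nor the randomisation factors in the primary model

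*Protocol article*

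**What the plan says.** Five places in the protocol article bear on this.

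- **Outcome.** Sample size: "The primary outcome variables of this study are the mean changes on the following indicators", followed by LDL cholesterol, resting systolic blood pressure, BMI and the PGWB. The hypotheses also express the expected effect, at least 0.3 SD, as a standardised difference between mean changes.
- **Adjustment.** Assessment procedure: "Adjusted change scores for all the outcome measures will be calculated". The covariates are not given. The same section says that demographic data, including gender, "will be assessed in order to control for these potential confounders".
- **Randomisation.** Randomization procedure and blinding: "A block randomization scheme is employed, balancing gender and baseline impact of modifiable cardiovascular risk factors", the risk factor being the INTERHEART score in two levels, highest against middle tertile.
- **Primary model.** The abstract says: "Treatment effects will be tested via multilevel modeling". Statistical analysis specifies partial nesting, the alpha and the software, but lists no fixed covariates.
- **Covariates in the analysis section.** They appear only as candidates for exploration: "the moderating effects of some putative covariates such as gender, age, level of education, marital status, cardiovascular disease status, and diabetes". The INTERHEART stratum is not among them.

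**The concern.** The sections do not tell one story. One defines the outcome as a change, one says the change will be adjusted for something unstated, and the one describing the primary model carries no adjustment forward. Control for gender is announced in one place and absent from the primary model in another. The second balancing factor is used to allocate patients and then not mentioned again.

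The word adjusted also has more than one possible meaning. Besides demographics, Assessment procedure names recurrent cardiac events and medication at each time point, some of which arise after randomisation. The moderator analyses are then built on whichever multilevel model proves best in the primary analyses, so the primary model itself may be open to choice during the analysis.

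At stake is precision. A change analysed without its baseline value as covariate is never more precise, in large samples, than the baseline-adjusted comparison. Balancing on prognostic factors and then leaving them out of the model gives standard errors larger than the design warrants. The trial has little power to spare, as the working shows.

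**Working it through.** **Inputs from the article.** Effect 0.3 SD on the scale of mean changes (hypotheses; Sample size). 160 patients before drop-out, so 80 per arm; power 0.80 at alpha .05 (Sample size). Two-tailed tests at 0.01, written as 0.05/4, which is 0.0125 (Statistical analysis). ACT groups of 8 (The ACTonHEART intervention).

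**Assumptions, because the article gives no figures.** rho, the correlation between baseline and 12-month values: 0.5, 0.7, 0.9. Equal variance s² at both times. ICC in the ACT arm: 0 in the main calculation, then 0.05 and 0.10.

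**Step 1: the plan's own figure.** n per arm = 2(1.960 + 0.842)²/0.3² = 174.4, so 175 per arm and 350 in total before any clustering. The stated 160 is not reproduced. With 80 per arm, power at 0.3 SD is 47.5% at alpha .05 and 24.9% at .01. The stated 160 fits an effect near 0.5 SD (88.5% at alpha .05 with no clustering).

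**Step 2: variance with and without baseline.**
- Change, unadjusted: 2(1 − rho)s²
- Baseline as covariate: (1 − rho²)s²
- Ratio: (1 − rho²)/[2(1 − rho)] = (1 + rho)/2

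**Step 3: power after adjustment.** Power = Φ(0.3/√(ratio × 2/80) − z), with z = 2.576 at alpha 0.01. Unadjusted: 0.3/√(2/80) = 1.897, and Φ(1.897 − 2.576) = 24.9%.

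| Assumed rho | Ratio | 160 patients worth | Power at .01 | Power at .05 | N for 80% at .05 |
|---|---|---|---|---|---|
| unadjusted | 1 | 160 | 24.9% | 47.5% | 350 |
| 0.5 | 0.75 | 160/0.75 = 213 | 35.0% | 59.1% | 262 |
| 0.7 | 0.85 | 160/0.85 = 188 | 30.2% | 53.9% | 298 |
| 0.9 | 0.95 | 160/0.95 = 168 | 26.5% | 49.5% | 332 |

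At alpha 0.0125 the power moves from 27.4% to 37.9%, 33.0% and 29.1%.

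**Step 4: clustering.** With standard error √(ratio × [(1 + 7 ICC)/80 + 1/80]) and alpha 0.01:
- ICC 0.05: 20.5% unadjusted; 29.0%, 24.9% and 21.8% adjusted (rho 0.5, 0.7, 0.9)
- ICC 0.10: 17.3% unadjusted; 24.5%, 21.1% and 18.4% adjusted

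The levels fall, but the ordering is the same.

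**Step 5: strata.** The gain from adding gender and INTERHEART tertile depends on how much outcome variance they explain. The article gives no such figure, so no number can be put on it.

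**The case against.** The strongest reply is that the article may already intend what is asked for. It announces adjusted change scores for every outcome, and baseline is a natural thing to adjust a change for. It announces control for gender. It lists no fixed effects at all, and an article commonly leaves such a list to the full protocol or analysis plan, neither of which is shown. A repeated-measures multilevel model with baseline among the responses could also recover much of the precision, and the model form is not stated. Finally, defining the outcome as a change does no harm in itself: once baseline is a covariate, change and follow-up value give the same treatment estimate.

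Most of this stands. A reader might infer that the outcomes are raw changes and that the analysis adjusts for nothing. The article does not support that, because adjusted scores are announced. Nor is gender mentioned only as a moderator. A reader might also infer that regression to the mean biases the comparison. It acts alike on both randomised arms in expectation; only chance baseline imbalance remains, and that is a matter of precision. That LDL cholesterol and systolic pressure would lose most has no figure behind it in the article.

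What the reply does not remove is the disagreement on the page: the adjustment is undefined, the section describing the primary model does not carry it, and one balancing factor is in no analysis. The point rests on that, not on the absence of a covariate list.

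**Conclusion.** The point holds as one of unclear and inconsistent specification, with a precision cost that is conditional. If the change is not baseline-adjusted, its variance is larger than it need be: adjustment would cut it by 25%, 15% or 5% for assumed rho of 0.5, 0.7 or 0.9. At the stated alpha of 0.01, with 80 per arm, 0.3 SD of change and no clustering, that is worth roughly 10, 5 or 2 percentage points of power over 24.9%. If the announced adjusted scores already use baseline, this gain largely disappears. The figures also rest on equal variances at both times.

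Omitting the strata makes inference conservative, not falsely positive, to the extent that the strata are prognostic; the amount is unknown. Adjustment does not repair the sample size: even at rho 0.5, 80% power at alpha .05 would need 262 patients. That shortfall comes from the effect size, the sample size and the alpha, and is a separate matter.

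**What to change.** Under Statistical analysis, state that the partially nested model for each primary outcome includes as fixed effects, in a single fit, the baseline value of that outcome, gender and the INTERHEART stratum used in randomisation, and that the treatment difference at 12 months is the estimate. The response may be the 12-month value or the change. In Assessment procedure, either replace the sentence on adjusted change scores with a reference to this model or define the term to match it, and make the statement on control for demographic confounders consistent with it. Gender can stay on the list of exploratory moderators as well.

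The cost is wording only. All study measures are completed before randomisation, and the INTERHEART score is already needed for eligibility and allocation.

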We hypothesize that participants in the usual care group will show mean changes in the aforementioned variables comparable to those founded in the GOSPEL study, while patients in ACT condition will achieve better results on these primary outcomes with a medium between-group effect size (a standardized mean difference between mean changes of at least 0.3 standard deviations is expected).

*Secondary hypotheses:* The intervention will also improve a number of secondary outcomes: *1.* adherence to a heart-healthy lifestyle (increased physical activity; improved dietary patterns, smoking status, medication adherence); 2. perceived health-related quality of life; 3. other biological indicators of cardiovascular risk (exercise capability during an incremental bicycle stress test, lipid profile, glycosylated haemoglobin level, and waist to hip ratio).

*Mediation hypotheses:* The intervention will improve levels of psychological flexibility and the change in this variable will be associated with change in outcome variables.

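### Under the stated inputs, 160 participants give about 47% power for a 0.3 SD effect at two-sided 0.05 before clustering, not the stated 80%, and about 25% or less at the planned per-outcome alpha of 0.01.

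*Protocol article*

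**What the plan says.** The Sample size section hypothesizes a medium effect and says at once what that means: "in particular a standardized effect of at least 0.3 standard deviations". It converts this into expected between-group differences at 12 months of "8.8 mg/dl in LDL cholesterol, 4 mmHg on systolic resting blood pressure and 1.3 kg/m^2^ in BMI". It then cites a source for the statement that "a clustered design will require 160 participants to detect medium treatment effects with a statistical power of 0.8 and a significance level of .05". After an allowance for drop-out the total is 168, "resulting in 84 participants being randomly assigned to each group".

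The scale of the effect is given twice. Study objectives and hypotheses says that "a standardized mean difference between mean changes of at least 0.3 standard deviations is expected". The Sample size section adds: "The primary outcome variables of this study are the mean changes on the following indicators".

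The Statistical analysis section sets the test level: "Two-tailed tests with an adjusted critical alpha of 0.01 (0.05/4) will be conducted". The ACT arm is treated in groups of 8 (The ACTonHEART intervention), and usual care is not grouped. The article gives no ICC and no baseline–follow-up correlation.

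**The concern.** Effect size, sample size, power and alpha are all printed, so the power claim can be checked. The only meaning the article gives to a medium effect is 0.3 SD, so the 80% attaches to 0.3 SD. A two-arm comparison with 80 per arm is well short of 80% power for a difference that small, and nesting patients in therapy groups lowers it further. The sizing also uses 0.05, whereas each primary outcome is to be tested at 0.01.

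What is at stake is how the result will be read. If the trial finds no difference, a reader who trusts the stated 80% would take this as fair evidence that differences of the listed size are absent. The stated inputs do not give the trial that sensitivity.

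**Working it through.** **Inputs from the article.** Standardized difference d = 0.3 on mean change; 80 evaluable per arm (160 in total, 1:1); two-tailed tests; alpha 0.05 for sizing and 0.01 for each primary outcome; therapy groups of m = 8 in the ACT arm only.

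**Assumed.** ICC of 0 to 0.10, because none is stated. The normal approximation is used. With only 80/8 = 10 therapy groups it is, if anything, generous.

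**Formulas.** With clustering in one arm, in SD units:

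- SE = sqrt[(1 + 7·ICC)/80 + 1/80] = sqrt[(2 + 7·ICC)/80]
- power = Φ(0.3/SE − z), with z = 1.960 at 0.05 and 2.576 at 0.01
- n per arm for 80% power at 0.05 = (1.960 + 0.842)² · (2 + 7·ICC)/0.3²
- effect detectable with 80% power = (z + 0.842) · SE

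**Attempt to reproduce the plan's figure.** At ICC 0, SE = sqrt(2/80) = 0.158 and 0.3/0.158 = 1.897. Power = Φ(1.897 − 1.960) = 47.5%; the noncentral t gives about 47%. The stated 80% is not reproduced. Other readings do not reach it either: 84 per arm with no drop-out gives 49.4%, and a one-sided 0.05 test gives 60.0%.

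**Results for d = 0.3 with 80 per arm**

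| ICC | SE | Power, 0.05 | Power, 0.01 | n per arm for 80%, 0.05 | Detectable SD, 0.05 | Detectable SD, 0.01 |
|---|---|---|---|---|---|---|
| 0 | 0.158 | 47.5% | 24.9% | 175 | 0.443 | 0.540 |
| 0.05 | 0.171 | 41.7% | 20.5% | 205 | 0.480 | 0.586 |
| 0.10 | 0.184 | 37.2% | 17.3% | 236 | 0.515 | 0.628 |

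The exact quotient 0.05/4 is 0.0125, which the plan rounds to 0.01. At 0.0125, power is 27%, 23% and 19% for the three ICCs, so the rounding does not change the picture.

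**Which effects fit 160.** At two-sided 0.05, 80 per arm gives 80% power for 0.443 SD at ICC 0, for 0.45 SD at ICC about 0.01, for 0.48 SD at ICC 0.05, and for 0.5 SD at ICC about 0.08. Several pairs fit, so the figure does not identify one effect.

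**On the outcome scales.** The listed differences imply SDs of 8.8/0.3 = 29.3 mg/dl, 4/0.3 = 13.3 mmHg and 1.3/0.3 = 4.33 kg/m². If these are SDs of change, the differences detectable with 80% power over ICC 0 to 0.10 are:

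| | LDL, mg/dl | Systolic pressure, mmHg | BMI, kg/m² |
|---|---|---|---|
| Listed in the article | 8.8 | 4 | 1.3 |
| Alpha 0.05 | 13.0–15.1 | 5.9–6.9 | 1.9–2.2 |
| Alpha 0.01 | 15.8–18.4 | 7.2–8.4 | 2.3–2.7 |

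**The case against.** The strongest defence is that the analysis may be more precise than a plain two-sample comparison. The article does not say where its SDs come from. The implied BMI SD of 4.33 kg/m² sits beside an expected usual-care change of only 0.4 kg/m², so the SDs may be those of single measurements and not of change. If so, a change-score analysis has variance factor 2(1 − r), where r is the baseline–follow-up correlation. At an assumed r = 0.7, power at 0.05 is 56–69% over ICC 0.10 to 0; at r = 0.9 it exceeds 95%. Reaching 80% before clustering needs r of about 0.77 (change score) or 0.74 (baseline adjustment). Even if the SDs are of change, the Assessment procedure section plans adjusted change scores. If that means baseline adjustment, an assumed correlation of 0.5 between baseline and change gives 59%, 52% and 47% at ICC 0, 0.05 and 0.10.

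This part stands: a reader might infer that each listed difference would be missed more often than found, and the article does not establish that. It would require an unadjusted analysis and SDs of change. The defence does not rescue the stated power, however. The article places the 0.3 SD on mean changes and neither states nor invokes a correlation.

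A second defence is that 160 rests on a cited source. The source is not at hand, so a reader who infers that 160 was computed for 0.5 SD goes beyond the document; that match depends on choosing an ICC near 0.08. But no source can make 160 sufficient for 0.3 SD under the inputs printed here.

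A third is that an article may leave details to a full protocol. That is fair for the ICC taken alone, but the point is a stated figure that does not hold, not an omission.

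**Conclusion.** The concern holds in this form: 160 participants do not give 80% power for 0.3 SD under the article's own inputs, and the shortfall is large. At 0.05, 350 evaluable patients (2 × 175) would be needed before clustering, more than twice 160.

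The no-clustering result needs no assumption beyond the printed inputs and an unadjusted comparison on the scale the article names. The clustered results rest on the assumed ICC range. A reader might take 37–47% to be the trial's true power, but it is not: those figures use 0.05, and the primary outcomes are tested at 0.01. Nor is any single-outcome figure the power for the primary hypothesis, which asks for success on at least two of four outcomes and so also depends on correlations among them that are not given.

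**What to change.** Keep the sample size and restate the claim in the Sample size section, in one of two ways:

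- Give the power for 0.3 SD at the alpha used for the primary tests: about 17–25% at 0.01, with 37–47% at 0.05 for comparison.
- Give the effect that 160 evaluable patients detect with 80% power: about 0.540–0.628 SD at 0.01, or 0.443–0.515 SD at 0.05.

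These ranges are for ICC 0.10 to 0 without baseline adjustment. State the ICC assumed. If a precision gain from baseline is relied on, state the assumed baseline–follow-up correlation and whether the SDs are of change or of single measurements, and recompute. The differences of 8.8 mg/dl, 4 mmHg and 1.3 kg/m² may remain as the hypothesis, but not as differences the trial has 80% power to detect.

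The cost is a rewording and a less favourable stated power. No patients are added.

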#### Study objectives and hypotheses

To the best of our knowledge this will be the first randomized controlled trial to evaluate the efficacy of ACT in cardiac patients. Thus, the main aim of this research is to examine the efficacy of a manualized ACT-group therapy program for preventing the long-term deterioration of several risk factors and lifestyle behaviors and for improving psychological well-being and quality of life in patients with IHD over a 12-months follow-up period. In order to reflect Medical Research Council recommended guidelines [50] as well as the multi-factorial nature of the intervention, a number of primary outcome measures will be considered.

Moreover, the study is aimed at exploring the mechanisms of change surrounding the intervention with increased psychological flexibility as a possible critical mediator of intervention effects.

Specifically, the current study is designed to test the following hypotheses:

Primary hypothesis: The proposed ACT intervention will be associated with significantly better achievement, compared to the usual care, in at least two of the following primary outcome measures: LDL-cholesterol, resting systolic blood pressure, body mass index, and psychological well-being measured by the Psychological General Well-Being (PGWB) Index.

As no RCT was available on ACT-based interventions for cardiac patients, at the time of the study design we were not able to predict the modification of these four outcome variables as effect of the intervention.

Otherwise, expected levels of change on some of these indicators can be projected for participants in the usual care condition based on the GOSPEL study [51], a recent Italian survey on a similar population. Results from this study showed time-related worsening of the management of cardiac risk factors at 12-months follow-up. In particular, in the usual care condition, the following mean changes from baseline to 12-months follow-up were observed: an increase of 0.4 mg/dl in LDL cholesterol levels, an increase of 0.4 Kg/m^2^ in BMI and a 15.2% decrease in the rate of patients at target for resting systolic blood pressure [51].

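### The stated 80% power, at a .05 level, is not the power of the primary hypothesis, which needs two of four outcomes, each tested at 0.01

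*Protocol article*

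**What the plan says.** Three sections of the protocol article bear on this point.

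- **Sample size.** The article adopts the convention that "a power level of .80 is considered adequate to detect treatment effects". It assumes a medium effect, "in particular a standardized effect of at least 0.3 standard deviations", and translates it into differences of "8.8 mg/dl in LDL cholesterol, 4 mmHg on systolic resting blood pressure and 1.3 kg/m^2^ in BMI"; no raw difference is given for the PGWB. Citing an outside source, it then says that "a clustered design will require 160 participants to detect medium treatment effects" "with a statistical power of 0.8 and a significance level of .05". After a dropout allowance of under 5% the total is 168, "resulting in 84 participants being randomly assigned to each group".
- **Statistical analysis.** "Two-tailed tests with an adjusted critical alpha of 0.01 (0.05/4) will be conducted for examining the treatment effects on the four primary outcomes".
- **Study objectives and hypotheses.** The primary hypothesis is "significantly better achievement, compared to the usual care, in at least two of the following primary outcome measures", the four being LDL cholesterol, resting systolic blood pressure, BMI and the PGWB.

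The sample size text contains no multiplicity adjustment and no joint criterion. Nowhere does the article connect the 80% to the 0.01 level or to the two-of-four rule.

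**The concern.** A reader will take 80% as the chance that the trial confirms its primary hypothesis if the intervention works as assumed. That chance depends on the per-outcome level, on the number of outcomes that must succeed, on how the outcomes correlate and on how many of them truly respond. The stated figure uses a different level and takes no account of the rest.

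This is not detail left to an analysis plan: the article itself gives the power, the test level and the success rule, and they do not fit together. If the true power is well below 80%, a result that misses the two-of-four rule could be read as evidence against the intervention when the trial had limited ability to meet that rule.

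**Working it through.** **Inputs from the article.** Evaluable N 160 (80 per arm); 168 randomised; power 0.80; planning level .05 (sidedness not stated, taken as two-sided); test level 0.01 two-tailed; success on at least 2 of 4; effect 0.3 SD; therapy groups of 8 in the ACT arm only (section on the ACTonHEART intervention).

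**Assumptions, not in the article.** ICC within therapy groups 0 to 0.10; a common correlation r between the four test statistics, 0 to 0.8; normal approximation.

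**Step 1: reproduce the plan's figure.** Per arm, n = 2(1.960 + 0.842)²/d². For d = 0.3 this gives 175, or 350 in total, before clustering. For d = 0.5 it gives 63, or 126. With the ACT-arm variance multiplied by 1 + 7 × ICC, 160 is reached at about d = 0.5 and ICC 0.075, neither of which is stated. So 160 does not reproduce from 0.3 SD. The dropout step does: 160 × 1.05 = 168.

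**Step 2: isolate the mismatch.** Grant the claimed 80% per outcome at two-sided .05. The expected test statistic is then 1.960 + 0.842 = 2.802.

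- Per outcome at 0.01: Φ(2.802 − 2.576) = Φ(0.226) = 59%. At 0.0125: Φ(2.802 − 2.498) = Φ(0.304) = 62%.
- At least two of four at 0.01, independent, all four responding, p = 0.589: 1 − 0.411⁴ − 4 × 0.589 × 0.411³ = 1 − 0.028 − 0.163 = 81%.
- With positive correlation, integrating the binomial tail over a shared normal factor:

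| Level | r = 0 | r = 0.2 | r = 0.4 | r = 0.8 |
|---|---|---|---|---|
| 0.01 | 81% | 76% | 72% | 65% |
| 0.0125 | 84% | 79% | 75% | 68% |

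- Fewer responding outcomes (independent, level 0.01; a null outcome succeeds in the right direction with probability 0.005). Three respond: 3p²(1 − p) + p³ = 0.633, plus about 0.0015 from the null outcome, so 63%. Two respond: p² = 0.347, plus about 0.005, so 35%.

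**Step 3: use the stated N and effect.** The expected statistic is d/√[(2 + 7 × ICC)/80]. For d = 0.3 it is 1.897, 1.750 and 1.633 at ICC 0, 0.05 and 0.10; for d = 0.5 it is 3.162, 2.917 and 2.722. All four outcomes are taken to respond, with r from 0 to 0.4.

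| d | ICC | One outcome, .05 | One outcome, 0.01 | Two of four, 0.01 |
|---|---|---|---|---|
| 0.3 | 0 | 47.5% | 25% | 26-28% |
| 0.3 | 0.05 | 41.7% | 20% | 19-22% |
| 0.5 | 0 | 88.5% | 72% | 85-93% |
| 0.5 | 0.05 | 83.1% | 63% | 77-86% |
| 0.5 | 0.10 | 77.7% | 56% | 68-77% |

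At 0.3 SD a single outcome at .05 already has under 50% power, before any adjustment or joint rule.

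**The case against.** The strongest reply is that the two departures pull in opposite directions. The stricter level lowers power for each outcome, while needing only two of four can give some of it back. With 80% per outcome at .05, four independent responding outcomes and a level of 0.01, the joint power is 81%, almost exactly the stated figure. At 0.5 SD the two-of-four power is 77-93% for ICC 0 to 0.05. This stands: the mismatch does not by itself prove that power is below 80%.

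A reader might also infer that the adjusted level and the two-of-four rule together pull power from 80% down to 19-28%. The documents do not support that. Those figures use 0.3 SD with 80 per arm, where one outcome at .05 already has only 47.5% (ICC 0) or 41.7% (ICC 0.05). Most of the deficit therefore belongs to the separate problem that 160 does not follow from 0.3 SD, and it should not be counted twice.

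Three further limits are fair. The Sample size section does not literally say that it concerns one outcome; that is inferred from its single effect size and unadjusted level. The effect is worded as a minimum of 0.3 SD, and 160 rests on a cited source that is not at hand. The test level still protects against false positives, since 0.01 is stricter than 0.05/4 = 0.0125.

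None of this makes the 80% the power of the primary hypothesis. Agreement at 81% needs full response and independence, neither of which the article states.

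**Conclusion.** The inconsistency is real, and the figure is wrong as a description of the primary hypothesis. The part due to the mismatch alone is moderate: from 80% per outcome at .05, the two-of-four power at 0.01 runs from about 81% to 65% over correlations 0 to 0.8 if all four outcomes respond. It falls to 63% if three respond and to 35% if two do (independent).

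The very low figures at 0.3 SD are correct arithmetic for the stated inputs but arise mainly from the size of 160. At 0.5 SD the joint power is near or above 80% unless the ICC approaches 0.10. All ranges rest on assumed ICCs and correlations and on the normal approximation. The type I error control of the planned tests is not in question.

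**What to change.** Keep 168 patients. In the Sample size section, state the power for the rule actually used: at least two of four outcomes significant at one fixed per-outcome level. Choose either 0.01 as tested or 0.0125 as 0.05/4 implies, and use it in both the power statement and the analysis. Compute it under partial nesting with groups of 8 in the ACT arm, over stated ranges for the ICC, the correlation between outcomes and the number of outcomes that respond. Retain the .05 calculation only as the labelled origin of 160, not as the power of the primary hypothesis.

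The cost is a short simulation and one rewritten paragraph. The downside is that the stated power falls, and at 0.3 SD it falls a long way. No extra patients are needed for this correction.
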